### 5.3 Other Outcomes of Interest

Workload:

- Frequency of daily and cumulated BG measurements per patient and in the cohort during the patient's enrolment period (duration of the ICU stay with a max of 15 days).
- Frequency of daily and cumulated adjustments of insulin and nutrition pump settings during the patient's enrolment period.

Compliance (only in intervention arm)

- Number of episodes per patient and in the cohort where a BG measurement is not followed up within 30 minutes by an accepted GS2 advice (during the enrolment period)
- Number of episodes per patient and in the cohort where GS2 advice was accepted by the nurse but pumps were not set according to the advice within 30 min by the nurse (nurse did not notice, was too busy, forgot, or misinterpreted advice = true errors)
- Number of advices given by GS2 which were accepted, accepted with modification or rejected

### 5.4 Safety Outcomes

Hypoglycaemia

- Overall number and percentage of mild ( $\leq 3.2$  mmol/l), and severe ( $\leq 2.2$  mmol/l) hypoglycaemic events per patient and in the study.
- Number and percentage of mild ( $\leq 3.2$  mmol/l), and severe ( $\leq 2.2$  mmol/l) hypoglycaemic events due to non-compliance (only in intervention arm)

Hyperglycaemia ( $> 8.5$  mmol/l)

- The time taken to normalize blood glucose will be the time from enrolment in the study to the time of the first of two consecutive BG measurements  $\leq 8.5$  mmol/l

- Percentage of time in the ICU with hyperglycaemia (BG > 8.5 mmol/l) before and after normalization per patient and in the cohort.
- Percentage of time in the ICU with hyperglycaemia (BG > 8.5 mmol/l) before and after normalization per patient and in the cohort due to non-compliance (only in intervention arm)
- Number of hyperglycaemic episodes after normalization per patient and in the cohort
- Number of hyperglycaemic episodes after normalization per patient and in the cohort due to non-compliance (only in intervention arm)

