Data were collected for four days. The BG target range 5-8 mmol/l. Nutritional targets were individually prescribed by the attending physician and were between 25-30 kcal/d per kg ideal body weight. The mean BG was significantly lower ( $7.0 \pm 1.2$  mmol/l) in Glucosafe patients than in control patients ( $8.0 \pm 1.2$  mmol/l). No adverse events including hypoglycaemia were reported in either group. In the intervention group, 170 (76%) measured BG values were in the 5-8 mmol/l target band, with the lowest BG value at 4.2 mmol/l. In the control group, 171 (51%) measured BG values were in the 5-8 mmol/l target band and the lowest BG was 4.0 mmol/l. The Glucosafe group was closer to isocaloric feeding ( $93.5 \pm 15\%$  of EE) than the control group ( $129.5 \pm 29.4\%$  of EE), but the difference was not significant.

e) In the third pilot study [34], Glucosafe's advice for insulin infusion was administered to 13 hyperglycaemic surgical and medical ICU patients and glycaemia was compared to the pre- and post-intervention days. The BG target range was 5-8.3 mmol/l. Nutrition was provided according to the department guidelines. Fig. 3 shows the cumulated BG measurements over the data collection periods.

[figure not shown]

Figure 3. Distribution of BG during 24h-preintervention (before), 12-14h-intervention (Glucosafe) and 24h-postintervention (after).

During Glucosafe intervention the mean and SD of BG ( $5.8 \pm 0.9$  mmol/l; N=99) was lower than during pre-intervention ( $7.8 \pm 1.8$  mmol/l; N=86) and during post-intervention ( $6.4 \pm 1.4$  mmol/l; N=56). No hypoglycaemic events occurred.

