## 5. CLINICAL INVESTIGATION OUTCOMES

### 5.1 Primary Outcome

Time-in-target (range: 5.0 to 8.5 mmol/l) per patient and in the cohort.

For the purpose of calculating time-in target, BG values are considered constant from one measurement to the next. The time-in-target is defined as the cumulative time in the 5 to 8.5 mmol/l range divided by the time from the first BG measurement to 2 hours after the last BG measurement.

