### 8.1.2 Control Intervention (standard/routine/comparator)

The current local protocols for glycaemia control and nutrition management will be used in the control group and in the historical control group for comparison.

After ICU admission, a BG measurement is performed. If glycaemia is in the accepted range (5.0-8.5 mmol/l) or spontaneously normal (4.0 to 5.5 mmol/l), no correction is proposed. In this case, a BG control should be done every 2 hours. In case BG measurements are twice  $> 8.5$  mmol/l, a new control is proposed in another sampling site. If the BG measurement is still  $> 8.5$  mmol/l, an IV insulin-therapy should be initiated following the local protocol. A further BG control should be done within the next 15-30 minutes until stability of the BG. Then, BG controls should be done every 2 hours. If BG measurement are  $< 4$  mmol/l, insulin-therapy should be stopped (if in progress) and a correction can be performed. A new control is done within 15 minutes. If the glycaemia is still under 4, a new correction is done. If the glycaemia is spent above 4, BG control are spaced to every 30 minutes. Then, when the glycaemia spent above 5, BG control are done every 2 hours. The algorithm of the local glycaemia control ICU protocol is presented in Figure 9.

[figure not shown]

Figure 9. Algorithm of the local glycaemia control ICU protocol (control and historical control group)

An estimation of caloric target is performed after the admission in the ICU. Then, if the patient stays more than 4 days and if the indirect calorimetry measurement is achievable, the measurement is performed, and the caloric target is adjusted. If gastro-intestinal tract is functional and there are no contraindications to enteral nutrition, it is started from day 1 with an appropriate solution regarding the pathologies and with an initial debit of 25 ml/h or 10 ml/h for a patient with severe shock (can be adapted according to tolerance). The 80-100% of the energy target need to be achieved at the end of day 3. If the energy target (80-100%) is not covered at day 4, a SPN (Supplemental Parenteral Nutrition) is indicated to cover the target.

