### **9.2.4 Assessment of safety outcomes**

#### Hypoglycemia

- Overall number and percentage of mild ( $\leq 3.2$  mmol/l) and severe ( $\leq 2.2$  mmol/l) hypoglycaemic events per patient and in the cohort
  - All hypoglycaemia episodes will be reported in the eCRF, number and percentage will then be calculated.

- Number and percentage of mild ( $\leq 3.2$  mmol/l) and severe ( $\leq 2.2$  mmol/l) hypoglycaemia events due to non-compliance (only in intervention arm)
  - o All hypoglycaemia episodes will be reported in the eCRF. Then, those data will be analysed jointly with the “non-compliance” outcomes.

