#### Hyperglycemia (> 8.5 mmol/l)

- Time to normalize blood glucose (the first two consecutive values values  $\leq 8.5$  mmol/l as indicator for normalization)
  - o All the BG measurements will be reported in the eCRF with the time of the measurement. The time to normalize BG will be analysed from those data for the control and the intervention group.
- Percentage of time in the ICU with hyperglycaemia (BG > 8.5 mmol/l) before and after normalization per patient and in the cohort
  - o BG values are considered constant from one measurement to the next. Percentage of time in the ICU with hyperglycemia is defined as cumulative time with BG > 8.5 divided by the time spent in the ICU.
- Percentage of time in the ICU with hyperglycaemia (BG > 8.5 mmol/l) before and after normalization per patient and in the cohort due to non-compliance (only in intervention arm)
  - o Percentage of time with hyperglycemia will be analysed jointly with the “non-compliance” outcome.
- Number of hyperglycaemic episodes after normalization per patient and in the cohort
  - o All hyperglycaemic events will be record in the CRF. Those data will be analysed jointly with the “Time to normalize BG” outcome.
- Number of hyperglycaemic episodes after normalization per patient and in the cohort due to non-compliance (only in intervention arm)
  - o All hyperglycaemic events will be record in the CRF. Those data will be analysed jointly with the “Time to normalize BG” and the “non-compliance” outcome.

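### The safety outcomes report time above target but no time below it, so a shift from above 8.5 mmol/l into the band between 3.2 and 5.0 would register there only as an improvement

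*Protocol*

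**What the plan says.** - **Primary outcome (section 5.1).** The outcome is "Time-in-target (range: 5.0 to 8.5 mmol/l) per patient and in the cohort". Glucose is held constant between measurements, and the cumulative time in range is "divided by the time from the first BG measurement to 2 hours after the last BG measurement". Too low and too high both count as out of target.
- **High side (sections 5.4 and 9.2.4).** Three measures: time to normalise, number of hyperglycaemic episodes after normalisation, and "Percentage of time in the ICU with hyperglycaemia (BG > 8.5 mmol/l) before and after normalization per patient and in the cohort". Section 9.2.4 defines the last as "cumulative time with BG > 8.5 divided by the time spent in the ICU".
- **Normalisation.** Sections 5.4 and 9.2.4 require two consecutive values at or below 8.5 mmol/l and give no lower limit. The synopsis requires two values between 5.0 and 8.5.
- **Low side (sections 5.4 and 9.2.4).** Counts only: "Overall number and percentage of mild" (at or below 3.2 mmol/l) and severe (at or below 2.2 mmol/l) events. Section 9.2.4 adds: "All hypoglycaemia episodes will be reported in the eCRF, number and percentage will then be calculated". The anticipated adverse device effect in 10.3.1 uses the same 3.2 limit.
- **Local care (section 8.1.2).** Below 4 mmol/l, "insulin-therapy should be stopped (if in progress) and a correction can be performed". The same section treats 4.0 to 5.5 as normal when it occurs spontaneously.
- **Safety aim (synopsis).** The main safety objective is to avoid hypoglycaemia and to reduce hyperglycaemia.

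**The concern.** The device advises on insulin, so its main safety question has two sides: does it reduce high values, and does it do so by overshooting? The safety outcomes answer the first in time and the second only through events at or below 3.2 mmol/l.

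A reading of 3.5 mmol/l would lead staff to stop insulin under the local protocol, yet it enters no hypoglycaemia outcome. Two such readings in a row would also satisfy the normalisation rule in 5.4 and so count as a success on the high side. An arm that exchanged time above 8.5 for time between 3.2 and 5.0 would look better on hyperglycaemia time and possibly on time to normalise, with nothing on the low side to set against it. No data safety monitoring committee is planned (section 1.6), so the reported safety outcomes carry more of the weight.

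**Working it through.** **1. What is disputed.** No stated figure is in dispute. The sample size in 11.2 is used only for its 68% (SD 21) time-in-target. It reproduces: 2 × (1.960 + 0.842)² × 21² / 10² = 69.2, so 70 per arm by the normal approximation; the t-test version gives 70.2, so 71.

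**2. Which outcomes register each band.**

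| Glucose (mmol/l) | Primary (5.1) | Safety (5.4, 9.2.4) |
|---|---|---|
| above 8.5 | out of target | time, episodes, delays normalisation |
| 5.0 to 8.5 | in target | normalised |
| 4.0 to below 5.0 | out of target | normalised; no low-side measure |
| above 3.2 to below 4.0 | out of target | normalised; no low-side measure |
| 3.2 or below | out of target | event count; meets the normalisation limit |

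**3. Effect of a shift.** Inputs: 68% in target (11.2), so 100 − 68 = 32% out of target. The protocol does not give the split into high and low, so time below 5.0 under standard care is *assumed* at 0, 4, 8 or 12%. Move 10 points from above 8.5 into the band above 3.2 and below 5.0:

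| Below 5.0 before | Above 8.5, before → after | Below 5.0, after | In target, after |
|---|---|---|---|
| 0% | 32 → 22% | 10% | 68% |
| 4% | 28 → 18% | 14% | 68% |
| 8% | 24 → 14% | 18% | 68% |
| 12% | 20 → 10% | 22% | 68% |

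The safety outcomes show a 10-point gain and no loss. If the 10 points came from the target range instead, time-in-target would fall to 58% and no safety outcome would worsen.

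**4. Does subtraction recover time below target?** Assume a true 68% in, 28% above and 4% below.
- 120 h glucose window in a 168 h ICU stay: hyperglycaemia time = 0.28 × 120 / 168 = 20%, so 100 − 68 − 20 = 12%, not 4%.
- 360 h window in a 480 h stay: 0.28 × 360 / 480 = 21%, so the remainder is 11%.
- Window equal to the stay: the remainder is 4%, which is correct.

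The window lengths are assumptions. Subtraction works only when the two denominators coincide.

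**5. Do the predecessor pilots show a low-side shift?** For the third pilot, section 3.3.3 reports "During Glucosafe intervention the mean and SD of BG" as 5.8 ± 0.9 mmol/l. The normal approximation is Φ((cut − mean)/SD), applied to the means and SDs in 3.3.3:

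| Pilot and period | Mean ± SD | Below 5.0 | Below 4.0 |
|---|---|---|---|
| Third, before | 7.8 ± 1.8 | 6.0% | 1.7% |
| Third, Glucosafe | 5.8 ± 0.9 | 18.7% | 2.3% |
| Third, after | 6.4 ± 1.4 | 15.9% | 4.3% |
| First, before | 8.6 ± 2.4 | 6.7% | 2.8% |
| First, Glucosafe | 7.0 ± 1.1 | 3.5% | 0.3% |
| Second, control | 8.0 ± 1.2 | 0.6% | below 0.1% |
| Second, Glucosafe | 7.0 ± 1.2 | 4.8% | 0.6% |

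The direction is mixed. In the third pilot the share below 4.0 is higher after Glucosafe than during it. In the first pilot both shares fall under Glucosafe. In the second both rise in the approximation, but the lowest observed values were 4.2 (Glucosafe) and 4.0 (control), so neither arm had a reading below 4.0. The result also depends on the distribution: a lognormal fit to the third pilot gives about 0.2% before, 1.0% during and 1.9% after for readings below 4.0.

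**The case against.** **This is an omission, and an analysis plan could add it.** The hypoglycaemia limits are used consistently, and an analysis plan that is not shown might add a below/in/above split. In part this stands. But the protocol itself fixes the safety outcome list and its definitions, and it is this fixed list that is one-sided.

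**Low readings are not invisible.** This stands. Every reading below 5.0 counts against the device in the primary outcome, and a downward shift lowers mean glucose, a secondary outcome (5.2). If time-in-target does not change, superiority is not concluded (11.4.2). A reader seeing less time above 8.5, unchanged time-in-target and a lower mean would suspect more time below 5.0. A reader might infer that these readings appear in no outcome at all, or that the trial could not tell overshoot from good control. The documents support neither. What is true is that no outcome identifies the readings as low. Partial masking, where time-in-target and low time both rise, is also still possible.

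**Advice below target is already watched.** Section 10.3.2 lists insulin advised while glucose is below 5 to 8.5 mmol/l, in a patient who is not insulin-dependent chronically diabetic, as advice giving rise to concern. That stands, but it covers advice, not the glucose that patients experience.

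**Much of the band is benign.** Section 8.1.2 calls 4.0 to 5.5 normal when spontaneous. This stands, and it puts the main weight on values above 3.2 and below 4.0.

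**The pilots.** It is tempting to read the roughly 19% below 5.0 in the third pilot as the size of a hidden effect. The documents do not support that: about 16 of those points lie between 4.0 and 5.0, the share after the intervention was nearly as large, and the first pilot's target range began at 4.4 rather than 5.0.

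**Conclusion.** The safety outcomes are asymmetric, and the point holds in that form. A shift of time from above 8.5 into the band above 3.2 and below 5.0 would reach them only as an improvement, point for point: 10 points moved is 10 points of apparent gain. The concern is strongest between 3.2 and 4.0.

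The 10-point shift and the 0 to 12% starting shares are assumptions that show the mechanism; they do not forecast what GS2 will do. The pilot figures are approximations to pooled readings and give no consistent evidence of more time below 4.0 under the predecessor. The primary comparison is not invalidated. This is a near-free improvement that bears directly on the stated safety objective.

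**What to change.** 1. Add to 5.4 and 9.2.4 the percentage of time with glucose below 5.0 and below 4.0 mmol/l, by arm, on the window and constant-between-measurements rule of 5.1.
2. Beside the primary result, report time below, in and above target on that same window, as three shares summing to 100%. The hyperglycaemia percentage over ICU time can stay as a separate outcome.
3. Reconcile the definition of normalisation in 5.4 and 9.2.4 (at or below 8.5) with the synopsis (5.0 to 8.5), so that time to normalise has one meaning.

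**Cost.** A few more descriptive safety variables to derive and present. All glucose values and their times are already recorded (9.2.1), so no new measurement is needed. The 5.0 and 4.0 cuts are taken from the protocol's own target range and local algorithm as reporting limits only; no clinical threshold or treatment rule changes.

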## **6. CLINICAL INVESTIGATION DESIGN**

### **6.1 General clinical investigation design and justification of design**

This study is an unblinded randomized controlled trial that aims to evaluate the performance and the safety of a new bedside tool: GS2 in comparison to the standard of care.

Data from the historical control group will be analysed retrospectively for 71 patients hospitalized in the ICU at the same period within 2 years before the study. The historical control group is included for two reasons. The first is to be able to assess cross-over effects. These may happen in the randomized control group, if the caregiver's behaviour in this group is influenced by the caregiver's exposure to the GS2 system, when the caregiver is using the system in the intervention group.

The second reason is to confirm the predictive accuracy of GS2. As described in section 3.3.1 there are modest differences between the prediction errors estimated from the three patient cohorts previously analysed with Glucosafe. It is therefore appropriate to confirm that the prediction error of GS2 is similar or smaller compared to Glucosafe's. In case the prediction error is smaller, it will be possible to reduce the frequency of blood glucose measurements, as described in IB 2.5 "Mechanisms of action". The frequency of blood glucose measurements is one of the outcomes for workload (section 9.2.3). This reduces workload and the amount of blood drawn from the patient. In case the prediction error is larger, it is a reason for discontinuation or modifications of the intervention, as noted in Section 2.9.

The analysis of data from the historical control group will start as soon as the authorization of the study has been obtained. Enrolment for the intervention and control groups will start when the retrospective analysis of the historical control group has been completed. Enrolment is expected to take 8 months. The data and the results will then be analysed and submitted for publication.

### **6.2 Methods for minimising bias**

#### **6.2.1 Randomisation**

Randomization (1:1) will be stratified by the gravity score APACHE II (mild/moderate/severe) and by the diabetic status (diabetes/non diabetic patients). A randomization list using block randomization with variable blocks size 2, 4, or 6 will be computer-generated by an independent statistician.

#### **6.2.2 Blinding procedures**

Not applicable.

#### **6.2.3 Other methods for minimising bias**

The study includes a historical control group to have an independent way of assessing possible "cross-over" effects from the intervention group to the control group. Historical controls' data will be retrospectively harvested from the patients' computerized record. They will be recruited within 2 years before the trial start.

### **6.3 Unblinding Procedures (Code break)**

Not applicable.

## 7. CLINICAL INVESTIGATION POPULATION

### 7.1 Eligibility criteria

Subjects fulfilling all the following inclusion criteria are eligible for the investigation:

All patients  $\geq 18$  years old admitted in adult ICU- Geneva with

- An expected length of stay  $\geq 72$ h
- At least 1 blood glucose (BG) measurement  $\geq 10$  mmol/l or 2 BG measurement  $\geq 8.5$  mmol/l
- Informed Consent signed by the subject/ legal representative, except for patients in the historical control group

The presence of any one of the following exclusion criteria will lead to the exclusion of the subject:

- Lack of legal consent or consent withdrawn, except for patients in the historical control group
- Pregnant or breast feeding\*
- Diabetic ketoacidosis or hyperosmolar state
- Oral feeding
- Fulminant hepatic failure
- Medically contraindicated to receive rapidly acting insulin by intravenous (iv) infusion or iv injection

\*A blood pregnancy test (blood beta-hCG) will be performed in all women of childbearing potential before entering the study.

### 7.2 Recruitment and screening

#### 7.2.1 Intervention and control groups

Screening for inclusion into the intervention and the control groups will be done once a day (Monday to Friday) expect for the run-in phase. If more patients respect the eligibility criteria, priority will be given to people whose relatives can be reached at first. Eligible and consent patients will be randomized to either intervention group or control group. A deadline of 24 hours will be given to the legal representative or to the independent physician after presentation of the study to give or not their consent. For patients, once they are capable of consenting, a 48-hour delay after presentation of the study will be given. Before inclusion, all patients are treated according to the ICU- Geneva Protocols.

We will perform a “run-in phase” for the first 3 patients randomized in the intervention group. For these patients, we will ensure that the user asks for one advice in GS2 after each blood glucose measurement. Daily, one of the co-investigators will extract the GS2 data and check that all the advice given concerning insulin and glucose are correct according to GS2 predefined settings and if these are clinically acceptable. After the run-in period, if the GS2 recommendations are considered clinically acceptable, the control will be spaced at once a week. In the event of problems noted, the daily control will be maintained.

#### 7.2.2 Historical control group

The patients in the historical control group will be recruited retrospectively as consecutive eligible patients, beginning within 2 years before the start of the recruitment into the intervention and the control groups.

### 7.3 Assignment to investigation groups

Once eligibility criteria have been verified and informed consent signed, patients will be randomized in one of the two study arms using randomization program in the secuTrial® platform.

### 7.4 Criteria for withdrawal / discontinuation of subjects

Once started in either intervention or control arm, the study protocol will continue until one of the following circumstances is encountered:

- 1- Death; or
- 2- Withdrawal of life support; or
- 3- Consent withdrawal

## 8. CLINICAL INVESTIGATION INTERVENTION

### 8.1 Identity of the medical device under investigation

#### 8.1.1 Experimental Intervention (medical device)

The name of the investigational product is GS2. The version used in the protocol is release 1.0 GMDN code: 61087. The name of the manufacturer is Aalborg University, Aalborg, Denmark. GS2 software is a medical device, which during the clinical trial will be installed at the bed-side computer running Centricity, which is the electronic Patient Data Management System (ePDMS) used in the ICU-Geneva. The function of GS2 is affected by the settings of GS2. The settings supplied by the manufacturer are given in Appendix 5, which contains a copy of the document GS2-Settings, which is a part of the Technical file for GS2. The GS2-Site-Acceptance-Test-Plan requires a review by the Sponsor to ensure that the settings used in the protocol are adapted to the workflow and to the requirements of the protocol. Modifications to the manufacturer's settings will be documented during installation of GS2.

GS2 is not CE marked as a Medical Device and an application for a pre-market approval for the study described in this protocol has been submitted to the Competent Authority, Swiss Medic.

Caregivers (physicians/nurses) will be advised by GS2 on glycaemic control and nutrition management of patients in the intervention group. The caregivers will be instructed in the use of GS2.

A patient randomised to the intervention group must be created as a patient in GS2. To do this one of the investigators must logon to GS2, which ensures the authentication and authorisation. The investigator then types in the Centricity ID of the patient, which initiates a search for the ID in Centricity. When a match for the ID is found, the patient's demographic data are automatically imported from Centricity, including name, ID, age, gender, weight, height, diabetes, admission date and time.

Once the patient has been created, GS2 can support the workflow for two different tasks: 1) Setting the nutritional targets and 2) Advising on nutrition and insulin therapy. A summary of these two tasks is given below. Further detail can be found in Instructions for Use (GS2-IFU).

[figure not shown]

Figure5. The two workflows supported by GS2: Setting the nutritional targets and advising on settings of nutrition and insulin therapy pumps.

